
### Follow-up

Potential perioperative adverse events of this research protocol will be followed up and evaluated in the PACU 2 h after surgery by an anaesthesiologist blinded to the assignment, which will include intraoperative awareness and local infection in electrode monitoring. Definitions and relevant plans are as follows:Intraoperative awareness: regaining consciousness during general anesthesia. Close monitoring of the BIS during surgery to prevent BIS values from exceeding 60. If such a situation occurs, the anesthesia will be immediately deepened.Local infection: strict aseptic procedures should be followed.

### Reporting of adverse events

All adverse events associated with this trial will be collected systematically and closely monitored until resolution or stabilization or until it has been shown that study treatment is not the cause of the event. The principal investigator of our team is responsible for reporting all adverse events to the Ethical Committee system of Beijing Tiantan Hospital. If adverse events occur, they will be immediately reported to the research department, and the principal investigator will be informed to determine the severity of the adverse events and decide whether to reveal the participant’s allocated intervention or terminate the trial according to the severity. All detected adverse events will be reported in trial publications. The definition of specific adverse events is listed at the above follow-up section.

### Data management

Dedicated persons will manage all the data. We intend to use the dual measure evaluation, dual data entry, and statistical analysis by double trained assessors to ensure the reliability and accuracy of the results. They will photograph all paper versions of the original materials and store them in an encrypted database. All electronic data will be stored in the electronic medical system of Beijing Tiantan Hospital. The electronic data of FVEPs will be saved in the Medtronic NimEclipse neuromonitoring system by the same neuroelectrophysiologist.

Patients’ personal information will be appropriately hidden, and only research-related data will be retained for statistical analysis. Paper materials, including the study protocol, case report form, and informed consent form, will be placed in a dedicated locked cabinet.

### Sample size calculation

We used PASS 15 to calculate the sample size for this study. According to the pre-experiment results, at 60 min after induction of anesthesia, the amplitudes of the LD group and HD group were 3.43 ± 0.78 μV and 2.37 ± 0.80 μV, respectively. According to the results of other studies, the superiority margin was defined as 20% of the N75-P100 amplitude in the HD group [6]. According to *α* = 0.025 and *β* = 0.2, a sample size of 63 cases can provide a superiority margin of 20% higher amplitude in the LD group than in the HD group. We conservatively set the dropout rate at 10% on the basis of actual 1.7% in our previous study, the sample size should be a total of 70 persons will be enrolled, and 35 patients in each group.

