## Background

Loss of vision during prone surgery is a devastating complication that occurs due to a variety of reasons [1]. Intraoperative prone position can cause mechanical damage or ischemia of visual structures, causing postoperative visual loss or visual field defects [2]. The flash stimulus is transmitted from the retina to the optic nerve, optic chiasm, optic tract, lateral geniculate body, optic radiation, and visual cortex and converted from a light signal to electrical conduction. The evoked potential waveforms and data extracted from the occipital lobe area during surgery are called FVEPs. They reflect the integrity of the visual pathway in real time to guide intraoperative decision-making and prevent visual impairment or deterioration of the same caused by visual pathway damage [3–5]. Previous studies have shown that the amplitude is the main measure for evaluating FVEP, in addition to the latency value. Recently, a study showed that setting the early warning value as the FVEPs’ amplitude decreased by 20% from the baseline can detect new quadrant blindness [6]. FVEPs have become a reliable method for intraoperative protection of visual function in procedures jeopardizing visual pathway integrity or visual function, such as spine surgery in the prone position, neurosurgery of the sellar region, and similar.

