The secondary endpoints are as follows:N75-P100 amplitude decline rate compared to baseline measured under TIVA, calculated by the formula $$\frac{\left[N75-P100\left(TIVA\right)-N75-P100\left(HD\right)\right]}{\left[N75-P100\left(TIVA\right)\right]}\times100\%$$ or $$\frac{\left[N75-P100\left(TIVA\right)-N75-P100\left(LD\right)\right]}{\left[N75-P100\left(TIVA\right)\right]}\times100\%$$. N75-P100 (TIVA) will be measured 30 min after anesthesia induction under TIVA in both groups. N75-P100 (HD) or N75-P100 (LD) will be measured 60 min after anesthesia induction in HD or LD group.P100-N145 amplitude decline rate compared to baseline measured under TIVA, calculated by the formula $$\frac{\left[P100-N145\left(TIVA\right)-P100-N145\left(HD\right)\right]}{\left[P100-N145\left(TIVA\right)\right]}\times100\%$$ or $$\frac{\left[P100-N145\left(TIVA\right)-P100-N145\left(LD\right)\right]}{\left[P100-N145\left(TIVA\right)\right]}\times100\%$$. P100-N145 (TIVA) will be measured 30 min after anesthesia induction under TIVA in both groups. P100-N145 (HD) or P100-N145 (LD) will be measured 60 min after anesthesia induction in HD or LD group.Rate of prolongation of P100 latency compared to TIVA baseline measurements, calculated by the formula $$\frac{\left[P100\left(HD\right)-P100\left(TIVA\right)\right]}{\left[P100\left(TIVA\right)\right]}\times100\%$$ or $$\frac{\left[P100\left(LD\right)-P100\left(TIVA\right)\right]}{\left[P100\left(TIVA\right)\right]}\times100\%$$. P100 (TIVA) will be measured 30 min after anesthesia induction under TIVA in both groups. P100 (HD) or P100 (LD) will be measured 60 min after anesthesia induction in HD or LD group.The success rate of FVEP monitoring is defined as the ratio of the number of eyes with a satisfactory waveform to the number of all monitored eyes.FVEP stacking satisfaction will be assessed by electrophysiologists. A satisfactory waveform that could be evoked no more than three times will be considered satisfactory.Intraoperative anesthetic and vasoactive drug dosage, including anesthetics (i.e., sufentanil, remifentanil, propofol, rocuronium) and vasoactive agents (i.e., atropine, ephedrine, noradrenaline, phenylephrine, urapidil)Recovery quality:Respiratory recovery time is defined as the time from the cessation of anesthesia to the patient’s spontaneous breathing.Eye-opening time is the time from anesthesia cessation to when the patient can be called to open their eyes.Extubation time is defined as the time from the cessation of anesthesia to the removal of the patient’s tracheal catheter.Post-extubation agitation score. Ratings will be performed immediately after awakening and 15, 30, and 60 min after awakening: 1 point—restful sleep; 2 points—awake and calm; 3 points—irritability or irritability or crying; 4 points—difficulty to comfort or uncontrollable crying; 5 points—unable to be quiet or confused or delirium.Post-extubation sedation score. Ramsay sedation scale will be administered to the patients immediately after awakening and at 15, 30, and 60 min after awakening: 1 point—awake but anxious and restless; 2 points—cooperation, orientation, quiet; 3 points—drowsiness and response to commands; 4 points—drowsiness, rapid response to tapping eyebrow or loud auditory stimuli; 5 points—lethargy, slow response to tapping eyebrow or loud auditory stimuli; 6 points—drowsiness, no response at all. Scores 2–4 indicate satisfactory sedation and 5 to 6 excessive sedation.

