### Statistical analysis

All data analyses will be performed on both a per-protocol (PP) and intention-to-treat (ITT) basis. The intent-to-treat population will include all subjects randomized to receive HD or LD anesthesia maintenance, and the completed FVEP data will be collected. The per-protocol population will include all subjects in the ITT population not identified as protocol violators (i.e., change in the anesthesia strategy after the trial initiates). These protocol violations will be shown in a listing. Subjects who do not obtain available FVEP data or abandon the study for various reasons will be considered to have failed HD/LD and will be excluded from any form of analysis. For the missing data, the last observation and the worst-case imputation scenarios will be used as the main interpolation method.

The statistical analysis will be performed by an independent statistician using SPSS V.25.0 (Somers, NY, USA). Histograms and the Shapiro‒Wilk test will be used to assess the normality of the data distribution. For the statistical description, the continuous variables will be presented as the mean (standard deviation, SD) for normally distributed data or median (interquartile range, IQR) for skewed distributions. Categorical variables will be reported as counts and percentages, and the relative risk with its 95% confidence interval (CI) will be calculated. The absolute standard deviation (ASD) will be determined to identify any imbalance in baseline characteristics.

The primary outcome (N75-P100 amplitude of FVEPs recorded 1 h after induction) will be analyzed using a superiority test. According to the results of other studies, the superiority margin was defined as 20% of the N75-P100 amplitude in the HD group [6].For secondary outcomes, *χ*^2^ tests or Fisher’s exact tests will be performed for categorical variables including N75-P100 amplitude decline rate, P100-N145 amplitude decline rate, rate of prolongation of P100 latency, success rate of FVEP monitoring, FVEP stacking satisfaction, adverse events related to FVEP monitoring, and recovery quality. Anaesthetic and vasoactive drug agent consumption will be analyzed using independent samples *t*-tests for normally distributed variables and Wilcoxon sum tests for variables with skewed distributions. The study will terminate after all the data for the last patient are collected.

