A 1-sided *P* value of 0.025 will be considered statistically significant for the primary outcome. If the confidence interval for mean differences of N75-P100 amplitude between LD and HD groups lied above the lower limit of *δ* with *P* < 0.025, we defined LD group will be superior to HD group. While all *P* values will be 2-sided with a significant level of 0.05 for the comparisons of N75-P100 amplitude decline rate, P100-N145 amplitude decline rate, rate of prolongation of P100 latency, success rate of FVEP monitoring, FVEP stacking satisfaction, anaesthetic and vasoactive drug agent consumption, and adverse events related to FVEP monitoring or recovery quality between the group LD and HD.

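### The 20% superiority margin is credited to a within-patient warning value, but the primary comparison is between arm means and cannot show whether either regimen takes patients past that value

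*Protocol article*

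**What the plan says.** The primary endpoint (Protocol article, Study endpoints) is the absolute N75-P100 amplitude 60 min after induction, compared between LD and HD. For that comparison, Sample size calculation says that "the superiority margin was defined as 20% of the N75-P100 amplitude in the HD group". It refers to results of other studies but cites only reference [6]. Statistical analysis repeats the definition and the citation, and requires the confidence interval for the LD-minus-HD mean difference to lie above δ. On significance it says: "A 1-sided *P* value of 0.025 will be considered statistically significant for the primary outcome".

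The Background describes reference [6] differently, as an early warning value under which "amplitude decreased by 20% from the baseline can detect new quadrant blindness".

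Change from baseline appears only among the secondary endpoints: "N75-P100 amplitude decline rate compared to baseline measured under TIVA". It is defined there as a percentage calculated from the 30-min TIVA reading and the 60-min reading. Statistical analysis then lists this decline rate among the categorical variables to be compared by χ² or Fisher's exact tests, and states no cut-off.

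**The concern.** The same 20% is attached to two different quantities. In the Background it is a change over time in a monitored patient, measured against that patient's baseline. In the margin it is a difference between the means of two separately randomised groups, expressed as a share of the lower mean. The article gives no reasoning that leads from one to the other.

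This matters because the stated aim is to find out whether the low-concentration regimen is suitable for FVEP monitoring. For that purpose it is relevant how often an anaesthetic regimen alone brings a patient to the warning value. If the margin is presented as resting on the warning value, a reader may take a positive trial as evidence on that question. The one endpoint that could address it, the decline from each patient's own baseline, is assigned to tests that cannot be applied to it as it is defined.

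**Working it through.** **Inputs.** From Sample size calculation: "the amplitudes of the LD group and HD group were 3.43 ± 0.78 μV and 2.37 ± 0.80 μV, respectively"; "According to *α* = 0.025 and *β* = 0.2"; 63 evaluable patients, 70 enrolled, 10% dropout, two equal arms. I take δ as fixed at the pilot HD mean. The article does not say whether the pilot or the observed HD mean will be used.

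**1. The plan's own figure.**
- Margin: δ = 0.20 × 2.37 = 0.474 μV.
- Expected difference: 3.43 − 2.37 = 1.06 μV. Distance above the margin: 1.06 − 0.474 = 0.586 μV.
- Normal approximation with SD 0.80, one-sided 0.025, power 0.80: n = 2 × 0.80² × (1.96 + 0.84)² / 0.586² ≈ 29.2, so 30 per arm. The non-central t calculation gives 31 per arm, 62 in total, against the stated 63.
- Dropout: 63 / 0.90 = 70.
- Power with 63 patients: SE = √[(0.78² + 0.80²) / 31.5] = 0.199; Φ(0.586 / 0.199 − 1.96) ≈ 0.84.

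The sample size agrees with the stated margin.

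**2. What the margin means as a reduction.** LD = 1.20 × HD is the same as HD = LD / 1.20, so HD is 1 − 1/1.20 = 16.7% below LD. That is the null boundary which a positive result excludes.

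**3. What has to be observed.** The whole interval must clear δ, so the observed difference must exceed about 0.474 + 1.96 × 0.199 = 0.864 μV. With HD held at 2.37 μV this is 0.864 / (2.37 + 0.864) = 26.7% below LD. If the true gap is exactly 16.7%, the chance of declaring superiority is 2.5%. The pilot gap is 1.06 / 3.43 = 30.9%.

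**4. Why the primary result does not speak to the warning value.** The article gives no mean TIVA amplitude, so its size is an assumption here. Hold the 60-min means at the pilot values and let the baseline mean B, taken as equal in both arms, vary. A group mean is at least 20% below B when B is at least that mean divided by 0.80: 2.37 / 0.80 = 2.96 μV for HD and 3.43 / 0.80 = 4.29 μV for LD.

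| Assumed baseline mean B | HD mean at least 20% below B | LD mean at least 20% below B | LD − HD |
|---|---|---|---|
| below 2.96 μV | no | no | 1.06 μV |
| 2.96 to below 4.29 μV | yes | no | 1.06 μV |
| 4.29 μV or more | yes | yes | 1.06 μV |

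The primary comparison is identical in all three rows, although they carry different messages about monitoring. The table works with group means only. How many individual patients cross the threshold also depends on the spread of their changes, which the primary comparison does not use either.

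**The case against.** The strongest defence is that the primary test is sound as it stands. Requiring the interval to clear a positive margin is stricter than ordinary superiority. The choice of margin neither inflates type I error nor biases the estimate, and readers can compare the means and interval with any threshold they prefer. The wording is also consistent within the article, since an LD amplitude 20% higher than HD is indeed 20% of HD. The decline from baseline is already the first secondary endpoint, and a cut-off for it could be left to an analysis plan not shown here. All of this stands as a defence of the test. It does not supply the missing link between reference [6] and the margin. Nor is the decline rate merely short of detail: a continuous percentage has been assigned to tests for categorical data.

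Two stronger readings are tempting, and the documents support neither.

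- A reader might infer that LD can be declared superior when HD is only 16.7% lower. The decision rule rules this out: 16.7% is the null boundary, and an observed gap of about 27% is needed.
- A reader might infer that the margin is simply taken on the wrong base, and that a 20% fall measured from LD would restore the cited cut-off. It would not. The article's baseline is each patient's TIVA reading, and LD patients also leave TIVA and may fall from it. No between-arm margin reproduces a within-patient cut-off.

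It is also fair to say that the article nowhere claims that a positive result shows HD reaching the warning value. The risk lies in what the citation invites.

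**Conclusion.** The point holds as a fault in the justification and scale of the margin. The only source cited for it describes a different quantity, and a positive result will establish that HD is more than 16.7% below LD and nothing about the warning value in either arm. There is no arithmetic error: 62 recomputed against 63 stated, and 70 after dropout. The primary test stays valid as a comparison of means.

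The conclusion rests on the article's own description of reference [6], which was not available to check. The agreement of the sample size assumes δ fixed at 0.474 μV. If δ were recomputed from the observed HD mean, testing LD − 1.20 × HD, the normal approximation gives 35 per arm before dropout.

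**What to change.** 1. In Study endpoints and Statistical analysis, prespecify for the N75-P100 decline rate the proportion of patients in each arm whose 60-min amplitude is at least 20% below their own 30-min TIVA baseline. Report it as a risk difference with 95% CI. This gives the planned χ² or Fisher test a defined outcome. Analyse the percentage decline itself as a continuous variable.
2. In Sample size calculation and Statistical analysis, describe the margin as the sponsor's choice, equivalent to HD 16.7% below LD, and stop presenting it as the warning cut-off of reference [6].

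**Cost.** No new measurements are needed, because both readings are already taken. The margin loses its stated clinical source. The binary endpoint has less power than the mean: with proportions near 50% (an assumption, and the least precise case) and 35 per arm, the 95% CI half-width is about 1.96 × √(2 × 0.25 / 35) = 0.23, or 23 percentage points.

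Recruitment began in July 2022 with completion estimated for June 2024, so this is a late change. It must be dated and submitted as a protocol modification by the route that the Ethics and dissemination section describes.

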### Statistical analysis

All data analyses will be performed on both a per-protocol (PP) and intention-to-treat (ITT) basis. The intent-to-treat population will include all subjects randomized to receive HD or LD anesthesia maintenance, and the completed FVEP data will be collected. The per-protocol population will include all subjects in the ITT population not identified as protocol violators (i.e., change in the anesthesia strategy after the trial initiates). These protocol violations will be shown in a listing. Subjects who do not obtain available FVEP data or abandon the study for various reasons will be considered to have failed HD/LD and will be excluded from any form of analysis. For the missing data, the last observation and the worst-case imputation scenarios will be used as the main interpolation method.

The statistical analysis will be performed by an independent statistician using SPSS V.25.0 (Somers, NY, USA). Histograms and the Shapiro‒Wilk test will be used to assess the normality of the data distribution. For the statistical description, the continuous variables will be presented as the mean (standard deviation, SD) for normally distributed data or median (interquartile range, IQR) for skewed distributions. Categorical variables will be reported as counts and percentages, and the relative risk with its 95% confidence interval (CI) will be calculated. The absolute standard deviation (ASD) will be determined to identify any imbalance in baseline characteristics.

The primary outcome (N75-P100 amplitude of FVEPs recorded 1 h after induction) will be analyzed using a superiority test. According to the results of other studies, the superiority margin was defined as 20% of the N75-P100 amplitude in the HD group [6].For secondary outcomes, *χ*^2^ tests or Fisher’s exact tests will be performed for categorical variables including N75-P100 amplitude decline rate, P100-N145 amplitude decline rate, rate of prolongation of P100 latency, success rate of FVEP monitoring, FVEP stacking satisfaction, adverse events related to FVEP monitoring, and recovery quality. Anaesthetic and vasoactive drug agent consumption will be analyzed using independent samples *t*-tests for normally distributed variables and Wilcoxon sum tests for variables with skewed distributions. The study will terminate after all the data for the last patient are collected.

A 1-sided *P* value of 0.025 will be considered statistically significant for the primary outcome. If the confidence interval for mean differences of N75-P100 amplitude between LD and HD groups lied above the lower limit of *δ* with *P* < 0.025, we defined LD group will be superior to HD group. While all *P* values will be 2-sided with a significant level of 0.05 for the comparisons of N75-P100 amplitude decline rate, P100-N145 amplitude decline rate, rate of prolongation of P100 latency, success rate of FVEP monitoring, FVEP stacking satisfaction, anaesthetic and vasoactive drug agent consumption, and adverse events related to FVEP monitoring or recovery quality between the group LD and HD.

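### Adverse events and recovery are compared in analysis sets defined by changes of anaesthetic and by availability of FVEP data, so neither set covers every exposed patient

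*Protocol article*

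**What the plan says.** All references are to the protocol article.

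- **Sets used.** Statistical analysis: "All data analyses will be performed on both a per-protocol (PP) and intention-to-treat (ITT) basis".
- **Per-protocol set.** The same section defines it as the ITT patients "not identified as protocol violators (i.e., change in the anesthesia strategy after the trial initiates"). That is the only kind of violation described, and changes made for the patient's safety are not exempted. On reporting, it says "These protocol violations will be shown in a listing".
- **Exclusion from both sets.** Patients with no usable FVEP data, or who abandon the study, "will be considered to have failed HD/LD and will be excluded from any form of analysis".
- **Outcomes covered.** The secondary outcomes to be tested include "adverse events related to FVEP monitoring, and recovery quality". The significance rule repeats this, setting a two-sided 0.05 level for "adverse events related to FVEP monitoring or recovery quality between the group LD and HD".
- **Handling of events.** Follow-up names two adverse events, awareness during surgery and infection at the electrode sites. On BIS above 60 it says: "If such a situation occurs, the anesthesia will be immediately deepened". Reporting of adverse events adds: "All detected adverse events will be reported in trial publications".

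**The concern.** A per-protocol set suits an endpoint such as the FVEP amplitude, where one may ask what the regimen does when it is followed. For harms, the event can be the reason the regimen was not followed. The patient then leaves the set because of the outcome being counted, and the arm in which this happens more often looks safer than it was.

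Both sets are also conditioned on having FVEP data, which has no bearing on whether a patient was exposed to desflurane or had an adverse event. At stake is the between-arm comparison of adverse events and recovery. The primary endpoint is not touched by this point.

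**Working it through.** No figure in the article bears on this point, so the check is mainly a reading of the rules against each other.

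**Step 1: do the rules reach safety and recovery?** Yes. The sentence on analysis sets is universal, and the same section names adverse events and recovery quality among the tested outcomes. A per-protocol comparison of both is therefore planned.

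**Step 2: can an adverse event cause removal from the per-protocol set?** In one route, yes.
- Awareness or BIS above 60 is answered by deepening (Follow-up).
- Anaesthesia regimen sets bands for each arm: desflurane 0.7–1.0 MAC with remifentanil in HD; desflurane 0.5 MAC with propofol 1.5–2.5 μg/mL and remifentanil in LD.
- Deepening inside a band is ordinary titration. A response outside the band, or with an added agent, could plausibly be classed as a change of strategy. That classification is an inference, since the article defines the term no further.
- Electrode infection would hardly cause a change.

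**Step 3: can recovery cause removal?** No. Under Study endpoints, the recovery times start when anaesthesia stops, and the agitation and sedation scores are taken after awakening. The per-protocol recovery comparison still selects on something that happened after randomisation, and the maintenance given may affect recovery.

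**Step 4: does ITT cover everyone exposed?** Not fully. It keeps a patient whose anaesthetic was changed only if FVEP data exist. The Remedy section says that patients whose FVEPs cannot be recorded stay in the study, yet Statistical analysis removes them from every analysis.

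**Step 5: how many might the FVEP and abandonment rule remove?** Assume that losses match the dropout rates in Sample size calculation. The planned 10% gives 0.10 × 70 = 7 patients. The 1.7% seen in the previous study gives 0.017 × 70 = 1.2, or about 1 patient.

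**Step 6: what could the per-protocol rule do to the comparison?** The event counts below are assumed purely for illustration, with 35 per arm as planned: 4 events in HD and 1 in LD. Relative risk (RR) = (events/n in HD) ÷ (events/n in LD). The ITT value is (4/35) ÷ (1/35) = 4.0.

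| HD event patients removed because of a change | HD per-protocol | LD per-protocol | RR | Fisher P |
|---|---|---|---|---|
| 0 | 4/35 = 11.4% | 1/35 = 2.9% | 4.0 | 0.36 |
| 2 | 2/33 = 6.1% | 1/35 = 2.9% | 2.1 | 0.61 |
| 4 | 0/31 = 0% | 1/35 = 2.9% | 0 | 1.0 |

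The first row shows that, if no event leads to a change, nothing moves. The choice of HD is arbitrary; the same would apply to LD. No row is near significance, so what is distorted is the estimate, not a test decision.

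**The case against.** The strongest reply is that little of the harm mechanism is documented, and much of that reply stands.

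- **Titration is part of the plan.** Both arms are adjusted to a BIS of 40–50, and deepening is itself instructed. A reader might infer that every such adjustment removes a patient. The text does not say so; only a change beyond the assigned regimen plausibly qualifies.
- **Haemodynamic trouble** might seem another route. The article answers it with vasoactive drugs and does not list it among the adverse events under Follow-up.
- **Recovery** cannot be the reason for a change, as its timing shows.
- **Nothing is deleted from the trial's record by the per-protocol rule.** ITT runs alongside, violations are listed, and all detected events are to be published. A reader might infer that the per-protocol tables contradict that publication promise. They do not: the promise can be kept without every table containing every event.
- **A named safety set, or a rule for choosing between discordant ITT and per-protocol results,** is commonly left to a statistical analysis plan or full protocol. Its absence from this article is not held against it.

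What does not fall is the stated rule. The article expressly sends the safety and recovery outcomes through both sets and expressly removes patients without FVEP data from everything. The mitigations disclose events; they do not supply a comparison in all exposed patients.

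**Conclusion.** The point holds in limited form. As written, the per-protocol comparison of adverse events can lose a patient because of the event, the per-protocol comparison of recovery is a post-randomisation selection, and ITT does not close the gap because it too depends on FVEP data.

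The direction of any bias depends on which arm has more event-driven changes, which the article does not indicate. Its size cannot be calculated, because no event rate or change rate is given. It is probably small: only one of the two named events has a plausible route to a change, and the previous study lost only 1.7%. The conclusion assumes that some responses to an adverse event would be classed as a change of strategy. The part about missing FVEP data needs no such assumption.

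**What to change.** Amend Statistical analysis in two respects.

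1. Limit the per-protocol analysis to the FVEP endpoints.
2. State that adverse events and recovery are compared by randomised arm in all patients who received any randomised maintenance anaesthetic, regardless of later protocol violation or availability of FVEP data. Any grouping by regimen actually received should be a sensitivity listing only.

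This takes one sentence and reduces the number of tables. Follow-up and recovery assessments are already planned, so it requires no new measurement. It leaves the primary analysis and the sample size as they are.

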### Remedy

If the FVEPs fail to record, neurophysiologists will check the stimulating apparatus and conditions, such as the stimulus intensity of light, intervals, and waves of ERG, to ensure light conduction and ascertain efficient delivery of retinal light stimulation [17]. The anaesthesiologists will check physiological parameters such as blood pressure, body temperature, and positioning. If an ideal FVEP waveform cannot be obtained after excluding all the above reasons, the surgeon will decide whether to continue the operation. Finally, if the FVEPs fail to record or the surgery is suspended, the patients will remain in the study, but the event will be recorded on the case report form.

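### Patients without available FVEP data are labelled failures of their regimen and then left out of every analysis, against the plan's own ITT and imputation rules

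*Protocol article*

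**What the plan says.** The Statistical analysis section of the protocol article contains three statements that bear on a patient whose FVEP cannot be recorded.

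- Analysis set: "The intent-to-treat population will include all subjects randomized to receive HD or LD anesthesia maintenance, and the completed FVEP data will be collected".
- Exclusion: patients from whom no usable recording is obtained, and those who leave the trial for whatever cause, "will be considered to have failed HD/LD and will be excluded from any form of analysis".
- Missing data, in the next sentence: "the last observation and the worst-case imputation scenarios will be used as the main interpolation method".

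The Remedy section deals with the same event at the bedside. After the equipment and physiological checks, "if the FVEPs fail to record or the surgery is suspended, the patients will remain in the study", and the event goes on the case report form.

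Under Study endpoints, the monitoring success rate is a secondary endpoint, "defined as the ratio of the number of eyes with a satisfactory waveform to the number of all monitored eyes". The primary endpoint is the N75-P100 amplitude 60 min after induction. The Background states that anaesthetic drugs can go as far as making FVEP extraction and interpretation fail.

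**The concern.** Losing the waveform after the switch to LD or HD is the extreme form of the amplitude suppression that the trial sets out to measure. A rule that calls this a failure of the regimen and then removes the patient selects on something that happens after randomisation and that the regimen may cause. Three things are at stake.

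- The success rate loses the patients in whom monitoring failed altogether.
- The amplitude comparison is made among patients who still had a waveform, so it no longer compares the randomised groups if failure differs between arms.
- Read literally, the exclusion also takes these patients out of the adverse-event, recovery and drug-use comparisons, none of which needs a waveform. Yet the section on reporting of adverse events promises that all detected events will be reported.

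**Working it through.** **The rules side by side.** Take a patient with a 30-min TIVA baseline and no recordable waveform at 60 min.

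- Under the ITT sentence the patient is randomised and belongs to the set.
- Under the exclusion sentence the patient is in no analysis.
- Under the missing-data sentence the 60-min value is imputed.

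The second outcome cannot hold together with either of the others. The last-observation option does not help: the only earlier value is the 30-min baseline, taken under TIVA before the allocated regimen starts (Anaesthesia regimen and Intervention sections). Carrying it forward would credit the regimen with an amplitude recorded before it was given.

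**Inputs** (Sample size calculation): LD 3.43 (SD 0.78) μV, HD 2.37 (SD 0.80) μV, margin 20% of the HD amplitude, one-sided α 0.025, power 0.80, 63 evaluable, 70 enrolled, 35 per arm. The protocol gives no recording-failure rate for desflurane, so every failure rate below is an assumption.

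**The plan's own figure.** Margin 0.2 × 2.37 = 0.474; excess over the margin 1.06 − 0.474 = 0.586 μV. A noncentral-t calculation gives 60 in total with SD 0.79 and 62 with SD 0.80, close to the stated 63; 63/0.9 = 70. The sample size is not at issue here.

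**Effect on the primary comparison.** Suppose amplitudes are normal, the lowest fraction f of HD is unrecordable, and no LD patient is. The mean of those left is 2.37 + 0.80λ, with λ = φ(z_f)/(1 − f). For f = 10%, λ = 0.195, the HD mean is 2.37 + 0.156 = 2.53, and the difference is 3.43 − 2.53 = 0.90.

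| f in HD only | HD mean reported | LD − HD reported | Excess over 20% margin | LD − HD with failures scored 0 μV |
|---|---|---|---|---|
| 0 | 2.37 | 1.06 | 0.586 | 1.06 |
| 1.7% | 2.40 | 1.03 | 0.545 | 1.07 |
| 5% | 2.46 | 0.97 | 0.482 | 1.10 |
| 10% | 2.53 | 0.90 | 0.399 | 1.16 |
| 20% | 2.65 | 0.78 | 0.250 | 1.31 |

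The changes from 1.06 are −3%, −8%, −15% and −26%. With the same f in both arms the reported difference stays at 1.05 to 1.06.

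A different model takes 2.37 as the mean of recordable patients only and scores a lost 10% of HD as 0 μV. The all-patient HD mean is then 0.9 × 2.37 = 2.13 and the difference 3.43 − 2.13 = 1.30. The rule would report 1.06, which is 0.237/1.297 = 18% lower. The size depends on the model; the direction is the same.

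**Effect on the success rate** (patient level, both eyes lost, none in LD):

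| HD failures | Success if kept, HD vs LD | Fisher p | Reported under the rule |
|---|---|---|---|
| 4/35 | 88.6% vs 100% | 0.11 | 31/31 vs 35/35 |
| 7/35 | 80.0% vs 100% | 0.011 | 28/28 vs 35/35 |

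The endpoint is defined per eye, so these patient counts only illustrate what the rule removes.

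**The case against.** There is a fair case for a narrower reading, and much of it stands.

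- **Imputation.** The exclusion could be meant for patients with no FVEP data at all, leaving a patient with a baseline but no 60-min value to worst-case imputation. The text allows this, but calling the excluded patients failures of HD/LD points the other way. The conflict therefore remains.
- **ITT clause.** A reader might infer that the ITT set is formally limited to patients with complete FVEP data. The clause is garbled and does not plainly say so. The restriction comes from the exclusion sentence.
- **Success rate.** A reader might infer that the endpoint becomes worthless or is fixed at 100%. It is not. It counts eyes, while the exclusion is by subject, so one-eye failures still count, as do waveforms that are recorded but unsatisfactory.
- **Remedy section.** Remaining in the study with the event recorded is not strictly incompatible with being left out of an analysis set. The two passages fit badly together; they do not flatly contradict each other.
- **Direction.** If failures gather in HD at low amplitude, dropping them works against LD. A reader might infer that the rule favours the hypothesis, and the documents do not support that.
- **Size.** The planners cite 1.7% dropout and 100% monitoring success in their earlier study. That success rate was obtained with sevoflurane at 0.5 MAC and TIVA, so it says little about desflurane at 0.7–1.0 MAC, but failures may well be few.
- **Scoring failures as 0 μV** makes the endpoint partly composite and widens its spread. With 10% zeros the HD variance is 0.9 × (0.80² + 2.37²) − 2.133² = 1.08, so the SD rises from 0.80 to about 1.04.

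**Conclusion.** The point holds as a wrongly stated rule. The exclusion sentence conflicts with the ITT and imputation sentences around it, and it removes patients because of an event that the protocol itself attributes to anaesthetics. The firm consequence is that whole-patient recording failures drop out of the success rate. With an assumed 7/35 HD failures and none in LD, a difference with p = 0.011 would vanish; with 4/35 the difference hidden would not have been significant anyway.

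Bias in the primary comparison is possible but conditional. It needs failure rates that differ by arm. With an assumed 10% low-amplitude loss in HD only, the reported difference is about 0.90 instead of 1.06 μV, to LD's disadvantage; with equal rates it is negligible. No false claim of LD superiority is shown.

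**What to change.** Reword the analysis-set paragraph as follows.

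1. Delete the clause that removes these patients from all analyses, and analyse all randomised patients as allocated.
2. Compute the success rate and stacking satisfaction on all monitored eyes of all randomised patients, counting a non-recordable waveform as a failure.
3. Keep these patients in the adverse-event, recovery and drug-use analyses.
4. For the primary outcome, do not carry the TIVA baseline forward when the waveform cannot be evoked after the checks in the Remedy section. Apply the plan's own worst-case rule and say what the score is, for example 0 μV or worst rank. Note that a rank score does not carry a margin expressed in μV.
5. Add a sensitivity analysis on recordable patients only.

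No new data are needed, because recording failures already go on the case report form. The cost is some extra analysis, together with a wider SD and a partly composite endpoint under a worst-case score.
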